### Sample size

The *primary superiority hypothesis* for this trial was powered based on a conservative estimate of HCV treatment initiation of 10% for clinician referral and a hypothesized increase to 30% (absolute increase of 20%) for those allocated to the linkage navigation intervention (Fig. 3). This trial was powered based on the < 40 years of age or IDU stratum to ensure adequate power overall. As such, it was estimated that a minimum of 140 participants (70 per arm) will be required in each stratum for a total of 280 participants to achieve a power of 80%, using an alpha of 0.0492 based on methods for one interim analysis by O’Brien and Fleming. Using the approach by O’Brien-Fleming, the interim analysis will occur at the study’s halfway point, after 140 total patients (approximately 35 per arm) have been enrolled and outcomes data collected, and with an effectiveness threshold of *p* < 0.0054 for the primary outcome. A non-binding futility threshold of *p* > 0.5 will be used for the primary outcome. If the trial is not stopped after the interim analysis, it will proceed to enroll the full sample (280) with a significance effectiveness threshold of *p* < 0.0492.

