### Statistical methods

Analyses will be performed using the intention-to-treat principle. Bivariate statistical tests will be used to compare variables, including results from the ACASI surveys between study groups. Given the randomized design, the primary comparison will include the absolute percentage difference and risk ratio with 95% CIs for initiation of HCV treatment (primary outcome) and will be tested using chi-square or Fisher’s exact test. Kaplan-Meier and Cox proportional hazard regression will be used to estimate associations between the interventions and outcomes when modeled using time-to-event as an outcome. One interim effectiveness analysis is planned and will be performed by the study’s biostatistician while maintaining blinding to study arm allocation. Using the approach by O’Brien-Fleming, the interim analysis will occur at the study’s halfway point, after 140 total patients (approximately 35 per arm) have been enrolled and outcomes data collected, and with an effectiveness threshold of *p* < 0.0054 for the primary outcome. A non-binding futility threshold of *p* > 0.5 will be used for the primary outcome. If the trial is not stopped after the interim analysis, it will proceed to enroll the full sample (280) with a significance effectiveness threshold of *p* < 0.0492. The unit of analysis will be the patient. Secondary analyses will include comparisons of all other outcomes by study arm with subgroup analyses for the stratum of individuals < 40 years of age or PWID, age, gender, race, ethnicity, income, and education level.

Additional secondary analyses were planned a priori to evaluate disparities and the effects of social determinants of health (SDoH) on linkage, treatment initiation, and SVR12. Multivariable logistic regression analyses will be used to estimate the associations between gender and study outcomes while adjusting for confounders, including but not necessarily limited to age, race, ethnicity, housing status, HCV knowledge, and willingness to engage in care. Additionally, effect modifiers (e.g., race, ethnicity and gender, age and gender) will be evaluated. The statistical approach will be variable centered and will use hierarchical multivariable logistic regression to estimate associations between SDoH characteristics and linkage to care, treatment initiation, and SVR12. We will use a theoretical framework and prior studies to inform covariate selection to assess the relationships between SDoH and the outcomes.

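### The O'Brien-Fleming thresholds 0.0054 and 0.0492 together spend about 0.0513 rather than 0.05; with the interim level kept, the final level should be about 0.0479.

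*Protocol article*

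**What the plan says.** The Sample size section sets the final level "using an alpha of 0.0492 based on methods for one interim analysis by" O'Brien and Fleming. It places the interim look "after 140 total patients (approximately 35 per arm) have been enrolled and outcomes data collected", "with an effectiveness threshold of *p* < 0.0054 for the primary outcome". If the trial is not stopped, "it will proceed to enroll the full sample (280) with a significance effectiveness threshold of *p* < 0.0492". The Statistical methods section repeats the same design and levels ("One interim effectiveness analysis is planned"; "effectiveness threshold of *p* < 0.0054 for the primary outcome").

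Both sections carry the same futility rule: "A non-binding futility threshold of *p* > 0.5 will be used for the primary outcome". The primary test is chi-square or Fisher's exact, and the effect is reported as the "absolute percentage difference and risk ratio with 95% CIs for initiation of HCV treatment". The Trial status section says that the interim analysis took place on August 1, 2022 and met no stopping rule.

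**The concern.** The purpose of a two-look boundary is that its two nominal levels together hold a fixed overall error rate. The article gives every input needed to check this: the number of looks, their timing, both levels, and the status of the futility rule. If the pair does not add up to 0.05, the final level is too lenient. A final p-value just under 0.0492 would then be declared significant under a rule that slightly exceeds 5%. This level decides the primary claim, and the article describes the final analysis as still to come.

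**Working it through.** **Inputs**
- Interim level 0.0054, two-sided: z = 2.782 (Sample size; Statistical methods).
- Final level 0.0492, two-sided: z = 1.967 (same sections).
- Information fraction t = 140/280 = 0.5 (Sample size).
- Two looks in all, with non-binding futility (both sections).
- Overall alpha 0.05, two-sided. This is an assumption, inferred from the lowering of the final level and from the 95% confidence intervals.

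**Step 1: reproduce the stated pair.** A classic O'Brien-Fleming boundary with two equally spaced looks uses z-values c√2 and c. The stated values give 2.782/1.967 = 1.4145, which is √2 to three decimals. So both levels come from one constant, c = 1.967, and the shape is as intended. What remains is whether that constant gives 0.05.

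**Step 2: overall error of the stated pair.** The two statistics are bivariate normal under the null, with correlation √0.5:

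1 − P(|Z1| < 2.782, |Z2| < 1.967) = 0.0513.

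The interim look spends 0.0054, so the final look adds 0.0513 − 0.0054 = 0.0459, where 0.05 − 0.0054 = 0.0446 is available. Varying both levels within their rounding moves the total only between 0.0512 and 0.0514.

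**Step 3: what would hold 0.05 at t = 0.5**

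| Condition | Interim p | Final p |
|---|---|---|
| Exact O'Brien-Fleming (c = 1.9774) | 0.0052 | 0.0480 |
| Interim kept at 0.0054 | 0.0054 | 0.0479 |
| Final kept at 0.0492 | 0.0026 | 0.0492 |
| Lan-DeMets spending, O'Brien-Fleming type | 0.0031 | 0.0490 |

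**Step 4: readings that might rescue the pair**
- Both levels read as one-sided p-values: total 0.0509.
- Futility treated as binding: total 0.0468, but the article calls the rule non-binding.
- A different information fraction: 0.0526 at 30%, 0.0520 at 40%, 0.0506 at 60%, 0.0500 at 70%. The pair holds 5% only from about 70% information upward, and the article fixes one half.

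**Step 5: the actual test.** Simulated overall error with chi-square, 70 then 140 per arm, 4 million runs:

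| Null rate | 0.0054 / 0.0492 | 0.0054 / 0.0479 | Difference (percentage points) |
|---|---|---|---|
| 10% | 0.0505 | 0.0505 | 0.003 |
| 20% | 0.0518 | 0.0507 | 0.10 |
| 30% | 0.0512 | 0.0496 | 0.16 |

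What remains above 0.05 after the correction comes from the discreteness of binomial counts, not from the boundary.

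**Step 6: effect on size and power.** For 10% versus 30%, moving the level from 0.0492 to 0.0480 changes the requirement from 62 to 63 per arm (72 to 73 with continuity correction). Power at 70 per arm moves from 84.7% to 84.4%. With 140 per arm it stays at about 99%.

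**The case against.** The strongest reply is that the defect is tiny. The excess is 0.0513 − 0.0500 = 0.0013, and the verdict changes only if the final p-value falls between 0.0479 and 0.0492. At the planned 10% control rate the correction hardly moves the chi-square error at all. This stands, and it limits the weight of the point.

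Second, Fisher's exact test is also allowed. With the stated levels its simulated overall error lies between 0.03 and 0.04 at null rates of 10% to 30%, well under 5%. So a reader who infers that the trial loses control of its error rate goes too far. But the article leaves chi-square open, and the levels have to hold for that option too.

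Third, both levels follow from one constant and agree across the two sections. The constant may come from a published source that is not shown here, so the documents do not establish a slip by the authors. That explains the numbers, but it does not make them add up to 0.05.

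Fourth, the overall 0.05 is never stated. It is an inference, though no other purpose for reducing the final level is apparent.

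Two stronger readings should be resisted. The mention of about 35 per arm might suggest a look at only 70 participants, which would enlarge the excess. The text fixes the look at 140 in total, and 35 per arm fits as the count per arm within each of the two strata (35 × 2 × 2 = 140). Also, a final p-value between the threshold and 0.05 could accompany a 95% interval that excludes no effect. The decision rule is stated separately and is unambiguous, so this is a matter of reporting preference, not an error.

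**Conclusion.** The point holds as a small numerical correction. At 50% information, with non-binding futility, the stated pair has an overall two-sided error of about 0.0513 against an inferred target of 0.05, an excess of about 0.13 percentage points. The result rests on that inferred target, on the stated look at 140 of 280, and on the chi-square option. The sample size and the design are unaffected, and the conclusion of the trial will rarely depend on the difference. It merits correction because the level governs the primary claim and is easily put right before the final analysis.

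**What to change.** Replace the final threshold of 0.0492 with p < 0.0479 in the Sample size and Statistical methods sections, and state that the overall two-sided alpha is 0.05. The interim level of 0.0054 should stay, because that look was planned at 0.0054 and is over. Before the final analysis, recompute the final level at the information fraction actually reached at the interim look, which the article does not report; 0.0479 applies to exactly one half. An interval at the matching level (95.2%) beside the 95% interval is optional.

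The cost is a change of wording and a slightly stricter final threshold, with negligible loss of power and no change to enrollment. The change can only make success harder to claim, so making it after the interim look should raise no concern about bias.

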**Fig. 3 Fig3:**
[figure not shown]
Sample size estimates for the DETECT Hep C Linkage-to-Care Trial

### Data collection

During this trial, an assessment of barriers and facilitators to linkage to HCV care will be conducted through use of an audio computer administered self-interview (ACASI) offered to all enrolled patients after informed consent has been obtained but before randomization. ACASI has been shown to be a superior method for collecting potentially sensitive information in an efficient and anonymous format [25]. The survey will be offered in English and Spanish and will collect the following data for all enrolled patients: (1) ED visit information (unique study identifier, date/time of the visit), (2) demographics (age, gender, race, ethnicity, primary language), (3) payer information (commercial, Medicare, Medicaid, self), (4) detailed contact information, (5) details of randomization, (6) clinician referral information, (7) HCV RNA testing, (8) linkage navigation details, and (9) all outcome measures. Data from (1) through (6) will be collected prospectively by a trained research assistant during enrollment, data from (7) will be collected retrospectively by a trained research assistant, data from (8) will be collected prospectively by the linkage navigator, and data from (9) will be collected by a trained research assistant, blinded to intervention allocation and distinct from the research assistant who will perform enrollment. All retrospective data collection will use structured methods. In prior HIV studies, we have consistently obtained longitudinal follow-up for > 90% of HIV-diagnosed patients from the ED thus we anticipate collecting similarly high HCV follow-up data [26, 27].

### Data management

Data will be entered into a secure electronic database (REDCap, Vanderbilt University, TN) that will be developed to maximize valid data entry by including closed-response entries and range restrictions [28]. Data will then be transferred into native SAS format and cleaned prior to performing analyses using the most current version of SAS (SAS Institute, Inc., Cary, NC). The dataset will be locked, and all analyses will be performed by the study’s biostatistician in conjunction with the principal investigators while blinded to study allocation.

### Statistical methods

Analyses will be performed using the intention-to-treat principle. Bivariate statistical tests will be used to compare variables, including results from the ACASI surveys between study groups. Given the randomized design, the primary comparison will include the absolute percentage difference and risk ratio with 95% CIs for initiation of HCV treatment (primary outcome) and will be tested using chi-square or Fisher’s exact test. Kaplan-Meier and Cox proportional hazard regression will be used to estimate associations between the interventions and outcomes when modeled using time-to-event as an outcome. One interim effectiveness analysis is planned and will be performed by the study’s biostatistician while maintaining blinding to study arm allocation. Using the approach by O’Brien-Fleming, the interim analysis will occur at the study’s halfway point, after 140 total patients (approximately 35 per arm) have been enrolled and outcomes data collected, and with an effectiveness threshold of *p* < 0.0054 for the primary outcome. A non-binding futility threshold of *p* > 0.5 will be used for the primary outcome. If the trial is not stopped after the interim analysis, it will proceed to enroll the full sample (280) with a significance effectiveness threshold of *p* < 0.0492. The unit of analysis will be the patient. Secondary analyses will include comparisons of all other outcomes by study arm with subgroup analyses for the stratum of individuals < 40 years of age or PWID, age, gender, race, ethnicity, income, and education level.

Additional secondary analyses were planned a priori to evaluate disparities and the effects of social determinants of health (SDoH) on linkage, treatment initiation, and SVR12. Multivariable logistic regression analyses will be used to estimate the associations between gender and study outcomes while adjusting for confounders, including but not necessarily limited to age, race, ethnicity, housing status, HCV knowledge, and willingness to engage in care. Additionally, effect modifiers (e.g., race, ethnicity and gender, age and gender) will be evaluated. The statistical approach will be variable centered and will use hierarchical multivariable logistic regression to estimate associations between SDoH characteristics and linkage to care, treatment initiation, and SVR12. We will use a theoretical framework and prior studies to inform covariate selection to assess the relationships between SDoH and the outcomes.

Although we do not anticipate significant missing data, multiple imputation will be used in instances where variables have > 5% missingness. No adjustments will be made for loss to follow-up as patients will be considered not linked to care after 18 months from the time of entry into the study.

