### Trial design

For this trial, we will perform a single-center prospective randomized two-arm parallel-group superiority trial to evaluate the effectiveness of two linkage-to-care strategies for patients newly identified with untreated HCV in the ED from the DETECT Hep C Screening Trial or through an active surveillance process of previously diagnosed patients (Fig. 2) [20]. Permuted block randomization with two strata (i.e., those less likely to initiate treatment: <40 years of age or active injection drug use (IDU) [defined as IDU within 30 days of enrollment] or those more likely to initiate treatment: ≥ 40 years of age and without active IDU) and varying block sizes will be used to minimize imbalance and to ensure appropriate numbers of patients in subgroups.

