Potential limitations of this trial include its performance at a single academic medical center with experience performing infectious diseases screening in the ED and with integrated linkage-to-care services for HIV, but not HCV. While the navigation standard work was developed using an interdisciplinary group of programmatic and content experts and based on prior processes related to HIV screening and other navigation programs, success of navigation may be limited by complexities of navigating care for patients who are socially and economically vulnerable. Furthermore, secular trends related to the diagnosis and treatment of HCV may influence the numbers of patients identified with active chronic HCV, which may limit the ability to enroll, and conducting this trial during the COVID-19 pandemic has led to unanticipated delays and disruptions, including varying trends in access to care and the broader use of telehealth, which may also affect results. Finally, although the hypothesized effect was influenced by existing knowledge and content expertise, very little prior data existed to inform the hypothesized effect; therefore, depending on the true effect, this study may be underpowered.

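### The primary comparison is unadjusted and leaves out even the prognostic randomization stratum: valid, but slightly conservative and less precise than the baseline data would allow

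*Protocol article*

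**What the plan says.** Under Statistical methods, the protocol article gives the randomized design as its reason for a simple two-group analysis: "the primary comparison will include the absolute percentage difference and risk ratio with 95% CIs for initiation of HCV treatment", which "will be tested using chi-square or Fisher’s exact test". It names neither a covariate nor a stratified test for this comparison.

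Other sections describe baseline information that could be used:

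- **Trial design** stratifies randomization into patients less likely to start treatment (under 40, or active injection drug use) and patients more likely to (40 or over, without active use).
- **Trial design** also gives two entry routes, "from the DETECT Hep C Screening Trial or through an active surveillance process of previously diagnosed patients". The route is known at enrollment.
- **Data collection** lists demographics and payer among the items recorded at enrollment. It also describes a survey of barriers and facilitators, "offered to all enrolled patients after informed consent has been obtained but before randomization".
- **Statistical methods** adjusts for "age, race, ethnicity, housing status, HCV knowledge, and willingness to engage in care" only in the secondary models of gender and outcome, where these variables are called confounders.

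The Discussion concedes that "depending on the true effect, this study may be underpowered".

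**The concern.** The protocol blocks on a factor because it expects that factor to predict the outcome, and then ignores it in the primary test. Blocking removes between-stratum variation from the true sampling error of the risk difference. The crude standard error still includes that variation, so the test is somewhat conservative and the interval somewhat too wide. Other enrollment variables may explain further variation, and chance imbalance in them stays in the crude estimate.

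At stake is precision within a fixed maximum of 280 patients, in a trial whose authors doubt their assumed effect. Validity is not at stake.

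**Working it through.** **Inputs.** From Sample size: "a conservative estimate of HCV treatment initiation of 10% for clinician referral", 30% with navigation, final alpha 0.0492, 80% power, 70 per arm in each of two strata, 280 in total. Sidedness is not stated; two-sided is assumed, so the critical value is z = 1.967. Stratum-specific rates and predictive strength are not given and are assumed below.

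**1. The plan's own figure.** With p̄ = 0.20,

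n = [1.967·√(2·0.20·0.80) + 0.842·√(0.10·0.90 + 0.30·0.70)]² / 0.20² ≈ 62 per arm, or 72 with continuity correction.

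Exact power at 70 per arm is 81.3% for Fisher and 80.2% for continuity-corrected chi-square. The stated 70 per arm is reproduced.

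**2. Crude power of the pooled comparison (140 per arm).** Power = Φ{[Δ√n − 1.967·√(2p̄q̄)] / √(p₁q₁ + p₂q₂)}.

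- 10% vs 30%: (0.20·11.83 − 1.113)/0.548 = 2.29, giving 98.9%.
- 10% vs 25%: 91.4% (92% by exact enumeration).
- 10% vs 22%: 78.3%.
- 10% vs 20%: (0.10·11.83 − 0.993)/0.50 = 0.38, giving 64.8%.

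**3. Leaving out the stratum.** Assume equal strata and exact balance. Under the null the crude test uses p̄(1−p̄), while the actual variance is the mean of p(1−p) over strata.

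- Control rates 5%/15% (mean 10%, as in the protocol): 0.0875/0.0900 = 0.972. The effective critical value is 1.967/√0.972 = 1.995, so the rejection rate is about 0.046.
- Control rates 5%/25%: 0.1175/0.1275 = 0.922. The effective critical value is 1.967/0.960 = 2.049, so the rejection rate is about 0.040.

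Simulation (100,000 runs) compared the crude test with the Cochran-Mantel-Haenszel (CMH) test:

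| Control rates | Null, crude | Null, CMH | Power at +12 points, crude | Power at +12 points, CMH |
|---|---|---|---|---|
| 5%/15% | 0.045 | 0.048 | 79.9% | 80.0% |
| 5%/25% | 0.042 | 0.050 | 70.4% | 72.5% |

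The stratum alone therefore gains between almost nothing and about 2 points of power, depending on how prognostic it is.

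**4. Adding other baseline variables.** If adjustment removes a fraction R² of the variance, the effective sample size is 280/(1−R²).

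| Assumed R² | Effective N | 10% vs 30% | 10% vs 22% | 10% vs 20% | 95% CI half-width at 10% vs 30% |
|---|---|---|---|---|---|
| 0 | 280 | 98.9% | 78.3% | 64.8% | 9.1 points |
| 2% | 286 | 99.0% | 79.1% | 65.7% | 9.0 |
| 5% | 295 | 99.2% | 80.4% | 67.1% | 8.8 |
| 10% | 311 | 99.4% | 82.4% | 69.4% | 8.6 |
| 20% | 350 | 99.7% | 86.6% | 74.5% | 8.1 |

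The half-width is 1.96·√(0.30/140)·√(1−R²).

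A direct simulation (6,000 runs per scenario) used a standardized logistic estimate with stratum, entry route, payer and a willingness score. At assumed baseline c-statistics of 0.64, 0.70, 0.75 and 0.80:

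- Variance relative to crude was about 1.00, 0.96–0.97, 0.90–0.91 and 0.81–0.84.
- Power for 10% vs 20% went from 65% to 65%, 67% to 68%, 66% to 70% and 67% to 73%.
- Power for 15% vs 25% went from 56% to 56%, 55% to 58%, 56% to 61% and 55% to 63%.
- Null rejection of the adjusted test was 4.6–5.0%.

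The simulated gain is thus 0 to 8 points. The 20% row of the table lies just beyond the strongest simulated case, which is why it shows almost 10 points at 10% vs 20%.

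**5. Overall type I error.** Bivariate-normal integration of the stated 0.0054/0.0492 pair gives 0.0513 at correlation √0.5 = 0.707 (crude at both looks). With a crude interim and an adjusted final statistic (correlation down to 0.644) it is at most 0.0519, a shift of about 0.0006.

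**6. Events available.** 14 + 42 = 56 at 10% vs 30%, and 14 + 28 = 42 at 10% vs 20%. The covariate list must be short.

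**The case against.** The strongest reply is that nothing here is an error. The crude comparison is unbiased and simple, its justification by randomization is sound, and it matches the test behind the sample size. At the design effect there is almost no power to gain. All of that stands.

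Three stronger readings are tempting, and the document does not support them.

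- **That the trial gives up important power at no benefit.** Crude power is about 99% at 20 points and 92% at 15 points. The loss matters only for effects of about 12 points or less. The Discussion's remark about power names no threshold, so it does not say that the trial is underpowered for any effect below 20 points.
- **That the protocol itself treats the survey items as predictors of starting treatment.** It calls them confounders of the gender association and gives no strength. Payer and entry route are nowhere described as predictors. Only the stratum is tied to likelihood of starting treatment.
- **That all these variables are at hand for everyone.** The survey is only offered, and enrollment may be by telephone after the visit. Housing, HCV knowledge and willingness do not appear in the itemized list under Data collection.

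A change now also carries a credibility cost. Trial status reports that the interim analysis has taken place, and Trial and data monitoring says there is no independent monitoring board. That calls for open labelling, and it does not rule the change out: the interim was to be run blinded to arm, and the effect on type I error is negligible.

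It might also be said that a blocked stratum is not worth adjusting for. That depends on its strength: with control rates of 5% and 25%, it restores the test level and adds about 2 points of power.

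**Conclusion.** The concern holds as a modest missed efficiency. The primary comparison, as explicitly fixed, omits both the prognostic randomization stratum and every other baseline variable. It remains valid, but it is slightly conservative (about 0.042 to 0.045 against 0.0492 under the assumed stratum rates) and less precise than it could be.

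At 10% versus 30% the benefit of adjustment is a narrower interval: a half-width of 9.1 points becomes 9.0 to 8.1 for R² of 2% to 20%. For true effects of about 12 points or less, the power gain is roughly 0 to 8 points.

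These sizes rest on a two-sided test, equal strata, exact balance within strata, complete covariates, and assumed stratum rates and predictive strength. Removing RNA-undetected participants after randomization would loosen the balance somewhat.

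**What to change.** Under Statistical methods, make the primary estimate a marginal risk difference and risk ratio from a standardized logistic regression with a robust standard error, tested at the stated final threshold. Adjust for:

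- the randomization stratum;
- entry route (newly identified or previously diagnosed) and payer, both available at enrollment;
- willingness to engage in care, only if it is largely complete, with missing values imputed by a method that uses neither arm nor outcome.

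Fix this list before the final data are unblinded, state that the change was made after the interim analysis, and keep the crude risk difference, risk ratio and chi-square or Fisher result as a supporting analysis.

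The cost is a change of wording and a little programming, with no new data, visits or patients. The estimands do not change. The downsides are small: the change follows the interim look, the list must stay short with about 42 to 56 expected events, and the gain is near zero if the predictors are weak.

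### The primary test ignores the two randomization strata that the protocol expects to differ on the primary outcome; a stratified test would be modestly more efficient at no cost in data

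*Protocol article*

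**What the plan says.** Under Trial design, the article plans "Permuted block randomization with two strata". One stratum holds patients under 40 or with injection drug use (IDU) within 30 days of enrollment, described as less likely to initiate treatment. The other is "those more likely to initiate treatment: ≥ 40 years of age and without active IDU". The stated purpose is that "varying block sizes will be used to minimize imbalance and to ensure appropriate numbers of patients in subgroups".

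Treatment initiation is the primary outcome. Under Statistical methods: "Given the randomized design, the primary comparison will include the absolute percentage difference and risk ratio with 95% CIs", continuing "for initiation of HCV treatment (primary outcome) and will be tested using chi-square" or Fisher's exact test. No stratification or adjustment is attached to this comparison.

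The stratum returns only in the secondary analyses, as "subgroup analyses for the stratum of individuals < 40 years of age or PWID". The logistic models in that section concern gender and social determinants of health, and the Cox model names no strata or covariates.

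**The concern.** Blocking within a prognostic stratum holds the arms nearly equal on that factor, so differences between strata contribute almost nothing to the chance variation of the arm difference. A pooled chi-square test still counts the between-stratum spread in its standard error. The standard error is then too large, the test rejects less often than its nominal level under the null, and the confidence intervals are wider than they need be. The article justifies the simple comparison by the randomized design, but that design is stratified, on a factor chosen for its expected relation to the primary outcome.

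What is at stake is precision and some power, mainly if the true effect is smaller than planned. The article's Discussion allows for this: it says little prior data informed the hypothesized effect and that the study may be underpowered.

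**Working it through.** **Inputs from the article (Sample size).** 10% versus 30%; 70 per arm in each stratum, 280 in total; 80% power; alpha 0.0492, taken as two-sided (critical z = 1.967).

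**Assumption.** The article gives no stratum-specific rates. I take 10% in the less-likely stratum, on which the trial was powered, and vary the other. One scenario uses 5%/25%.

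**1. The plan's own figure.** With mean rate 0.20,
n = [1.967·√(2·0.20·0.80) + 0.842·√(0.10·0.90 + 0.30·0.70)]² / 0.20² = 62 per arm, or 72 with continuity correction. Exact power at 70 per arm is 80.2% for the continuity-corrected chi-square and 81.3% for Fisher. The stated 70 is therefore consistent with a single-stratum calculation. With both strata pooled (140 per arm) at 10% versus 30%, power is 98.9%.

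**2. Size of the pooled test.** Let p1 and p2 be the control rates in two equal strata and p̄ their mean. The pooled test uses p̄(1−p̄); the variance that blocking leaves is the average of p1(1−p1) and p2(1−p2). With R the ratio of the second to the first, true size ≈ 2[1 − Φ(1.967/√R)].

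At 10%/40%: p̄(1−p̄) = 0.25·0.75 = 0.1875; within-stratum average (0.09 + 0.24)/2 = 0.165; R = 0.88; 1.967/√0.88 = 2.097; size 0.036.

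Simulation (at least 400,000 trials per scenario, 70 per arm per stratum, interim look ignored) compares the uncorrected pooled chi-square with CMH:

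| Control rates | R | Pooled size, formula | Pooled size, simulated | CMH size, simulated |
|---|---|---|---|---|
| 10%/20% | 0.980 | 0.047 | 0.048 | 0.049 |
| 10%/25% | 0.961 | 0.045 | 0.046 | 0.049 |
| 10%/30% | 0.938 | 0.042 | 0.042 | 0.049 |
| 10%/40% | 0.880 | 0.036 | 0.036 | 0.049 |

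Fisher's exact test on the pooled table would be more conservative still.

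**3. Power, same absolute effect in both strata.**

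| Effect | Control rates | Pooled | CMH |
|---|---|---|---|
| +20 points (planned) | 10%/20% | 97.7% | 97.7% |
| +20 | 10%/30% | 96.2% | 96.7% |
| +20 | 10%/40% | 95.4% | 96.3% |
| +12 points (assumed) | 5%/25% | 70.4% | 72.4% |
| +12 | 10%/40% | 58.6% | 63.2% |
| +10 points (assumed) | 10%/10% | 66.1% | 65.6% |

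The last row is the price of stratifying when the strata do not differ.

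**4. Removals after randomization.** Eligibility criteria exclude randomized patients whose HCV RNA proves undetected, so the blocks are not intact in the analysed set. With an assumed 30% removed at random, the pooled size at 10%/40% rises from 0.036 to about 0.040; CMH stays at about 0.049.

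**The case against.** The strongest reply is that nothing here is invalid. A reader might infer that ignoring the strata biases the result or inflates the type I error. It does neither: the error is on the conservative side.

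A reader might also infer that the omission endangers the trial's power. At the planned 20-point effect it does not. The trial was sized to give 80% power in one stratum, so the pooled comparison has ample reserve and stratifying adds 0 to 1 point. The larger gains need both a smaller effect and a wide gap between strata. The article calls the strata less and more likely to initiate treatment but gives no rates, so calling them strongly prognostic goes beyond the text. Removals for undetected RNA shrink the conservatism further. All of this stands, and it limits the weight of the point.

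On the subgroup, a reader might infer that the label PWID (person who injects drugs) defines a different group from the 30-day IDU criterion and so mixes the two randomization strata. The article does not support that. It calls the subgroup the stratum, shortens the criterion to IDU elsewhere, and gives PWID no separate time window. Shorthand is the natural reading.

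Finally, the interim analysis took place on August 1, 2022, so changing the primary test is more than an edit of wording. That also stands. What remains is that the article names the test, that it is the less efficient choice for this design, and that the alternative costs almost nothing in power if the strata turn out alike.

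**Conclusion.** The point holds as a matter of efficiency, not validity. The direction is certain if the strata differ as the article expects; the size is not, because the stratum rates are assumed. The loss of size is negligible at a 10-point gap and material from about 30 points. The power gain from stratifying is immaterial at the planned effect. It reaches about 2 to 5 points at a 12-point effect when the strata differ by 20 to 30 points. These figures assume equal strata of 70 per arm, a constant absolute effect across strata and no interim look. The change is worth making, but the trial's conclusions do not hang on it.

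**What to change.** - Make the primary test a Cochran-Mantel-Haenszel test stratified by the stratum recorded at randomization.
- Report the Mantel-Haenszel risk difference and risk ratio with confidence intervals.
- Stratify the Cox model by the same factor.
- Keep the pooled chi-square or Fisher test as a sensitivity analysis.
- As a minor wording matter, label the subgroup as the stratum recorded at randomization (under 40 years or IDU within 30 days) instead of using PWID.

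No new patients or data are needed, since assignment was made from stratum-specific sequences held in REDCap. Because the interim analysis has been done, the change needs a dated amendment, made before the final data are unblinded, that gives the reason and records who had seen interim results.
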